## Detailed information on the module content

### Module 0: Introduction

The aim of this module is to act as a frame for the intervention. In this module, participants are introduced to the intervention content, structure and its goals. Additionally, the participants are informed about how to contact the study team and are provided with resources in case of emergencies (a collection of phone numbers for emergency services).

### Module 1: Energy Management

This module focuses on fatigue as the most common symptom of PCC and how post-exertional malaise (PEM) can impact daily life. Participants are presented with exercises on how to monitor and better manage their energy levels, and how to deal more effectively with fatigue or exhaustion. Patients are instructed to only do exercises that their energy levels allow and, if in doubt, contact the study personnel or skip the exercise.

## ***Module 2: Healthy Lifestyle***

This module focuses on healthy nutrition in general and in the context of PCC, as well as mindful media consumption and exposure to information about PCC and their possible impacts.

## ***Module 3: Physical Activity***

This module focuses on how physical activity can be adjusted in order to better manage PCC symptoms. It covers strategies (i.e. pacing) and includes a video series about breathing techniques and relief positions for easier breathing, as well as exercises to manage physical symptoms and adjust activities of daily living in order to better deal with PCC related impairments.

## ***Module 4: Wrap-Up Week 1***

The content for this module is based on the feedback of the participants about the exercises from modules 1, 2 and 3 (see Standardized feedback questions; CRF). Those exercises that have been evaluated as most useful to the individual participant are sent via chat function for them to repeat. Participants also have the opportunity to complete unfinished modules during this time.

## ***Module 5: Mental Health***

This module consists of a video series about steps to improve mental health and covers the topics of anxiety, depression, management of physical symptoms, change of unwelcome thoughts and the power of social support in the context of PCC. It focuses on supporting participants to build better resilience and add to their strategies and techniques in dealing with PCC related psychological challenges.

## ***Module 6: Acceptance***

Based on principles of Acceptance- and Commitment Therapy (ACT), four key elements of acceptance are presented (acceptance and avoidance, understanding of cognitive fusion, the inner observer, and the value compass). The module offers exercises and promotes self-reflection regarding the participants' situation and condition.

## ***Module 7: Selfcare***

This module focuses on the importance of self-care and self-compassion and how to overcome the "inner critic". It contains a guided reflection exercises about their individual impairment caused by PCC and how they can better deal with the negative thoughts and emotions connected to it. A written exercise furthermore helps them distance themselves from the negative impact of PCC and presents them with a technique to better practice selfcare in their daily lives and activities.

## ***Module 8: Wrap-Up Week 2***

Similarly to Module 4, this module's content is based on participants' feedback on the exercises of Modules 5, 6, and 7. The exercises evaluated as most helpful and/or useful are sent via the chat function.

## ***Module 9a: Sleep***

Participants are presented with the core principles of sleep hygiene. Exercises to deal with sleep disorders (e.g. insomnia, parasomnia) and relaxation techniques to more easily fall sleep are also presented. Participants are encouraged to try out these exercises if necessary and applicable to their situation.

## ***Module 9b: Neurocognitive Impairment***

This module focuses on exercises to train and improve brain functions that are commonly impaired by PCC (i.e. memory, working memory, concentration and attention, and executive functions). Participants are guided through the variations and options regarding a wide variety of possible exercises in terms of choice, planning, execution and reflection.

## ***Module 9c: Pain Management***

Participants allocated to this module are presented with information relating to the mechanisms of pain and how it relates to PCC. The module contains additional information regarding strategies of pain management and relaxation exercises and participants are reminded of such exercises that they have encountered in past modules (e.g. breathing exercises and relief positions in

Module 3). They are guided through choosing, planning, executing and providing feedback about this content.

#### **Module 10: Stress Management**

This module focuses on different types of stress and the consequences of it. Participants are guided through evidence-based techniques in stress management (i.e. progressive muscle relaxation (PMR) and are presented with two exercises designed to recognize stressors and adjust their behavior accordingly to minimize stressful situations and improve overall well-being.

#### **Module 11: Motivation and Hope**

This module focuses on expectations regarding symptoms and the future course of PCC. Participants are instructed to imagine their lives in a year and are guided through steps to better adjust their prediction and manage their expectations in relation to PCC with the goal of having a more positive view on the future.

#### **Module 12: Conclusion**

This module concludes the digital intervention. Participants are asked to review the past weeks and months and reflect on their progress, the changes and the different techniques, strategies and psychoeducational content they have encountered. Furthermore, they are presented with a 10-step guide that is designed to help make meaningful and lasting changes to their habits and to better adjust to PCC.

### **3.4 Withdrawal and discontinuation**

Participants' participation in the study is voluntary and participants can withdraw their consent at any time without giving reasons. Their treatment/routine care will not be affected by this decision. Patients who drop out before T3 will receive a proportionate compensation of the CHF 50 they receive after completing T3. Patients completing all measures a second time (see 3.1) will receive this compensation again. Patients who withdraw their study consent/who drop out of the study will be asked for consent to analyze their encoded data up to the point of consent withdrawal/dropping out of the study. If they decline, their data will be deleted. After analyses, personal information of withdrawn participants (stored in a separate, password-protected document) will be deleted.

#### **DiLCoS Substudy**

Participation in the substudy is voluntary and consent can be withdrawn at any time without providing reasons. Patients' treatment/routine care will not be affected by this decision and it will not affect their participation in the larger BALCoS study itself. Patients who withdraw substudy consent or who drop out of the substudy will be offboarded from the platform and can no longer access study material or log in to the smartphone application. Patients who withdraw their study consent/who drop out of the study will be asked for consent to analyze their encoded data up to the point of consent withdrawal/dropping out of the study. This also means that their registration data will stay on the platform until the final data export, however, they will not be contacted again. If they decline, all their data will be deleted.

## **4 STATISTICS AND METHODOLOGY**

### **4.1. Statistical analysis plan**

As this is a registry-based cohort study, no formal sample size calculation is required. In the PCC outpatient clinic at the UHB, a total of 173 patients has been seen during the first year. Due to the constant changes in SARS-CoV-2 viral variants and the changing immune status of the population, it is not possible to definitely predict how many patients will visit the PCC outpatient clinic in the future. At this time, similar numbers of patients per year and consent of approximately 80% of patients are anticipated, resulting in around  $N=136$  patients per year enrolled in BALCoS.

Data will be analyzed in RStudio (Racine, 2012) or other statistical software packages. For baseline comparisons, continuous data will be reported as mean  $\pm$  standard deviation or median (interquartile range) and assessed means of analyses of variance (ANOVA), using general linear model (GLM)-family based procedures and Mann-Whitney U tests, depending on the variable distribution. Categorical variables will be described as counts (percentage) and compared using chi-square tests. For longitudinal and other data analyses, state-of-the-art procedures, such as generalized (mixed) models will be calculated to assess both within- as well as between-patient changes.

### **DiLCoS Substudy**

A power analysis was performed using G\*Power 3.1 (Faul et al., 2007). Assuming a power ( $1-\beta$ ) of 0.80,  $\alpha = 0.05$ , and a small to medium effect size of  $f = 0.15$  in a repeated measures, within factors ANOVA with two time points resulted in  $N=105$  participants. This estimation took a possible dropout rate of 15% into account. To have sufficient power for secondary analyses, this sample size is considered as the minimal sample size and more patients will be enrolled, if feasible during the data collection phase (first patient in March 2024, first patient out February 2025; last patient in March 2025, last patient out March 2026).

The primary analysis is a pre-post comparison of the primary and secondary endpoints (see section 2.2 Primary and secondary endpoints), with T0 as a pre-intervention measure and T1 as a post-intervention measure.

As a secondary analyses, T2 and T3 will be analyzed as follow-up measures to investigate the time-stability of intervention effects. Further, a comparative analysis (DiLCoS - treatment as usual) may be performed: Patients who participated in the BALCoS study before the initiation of the DiLCoS substudy as well as patients who agree to participate in BALCoS but do not give consent to participate in DiLCoS will be considered as a non-randomised control group. This will help in distinguishing the specific effects of the DiLCoS intervention to get a comprehensive understanding of the efficacy of the digital intervention. With these two groups, generalized mixed models will be calculated to assess both within- as well as between-patient changes.

Lastly, results from the DiLCoS substudy might serve as an additional arm to another intervention study conducted within the EU consortium (AIR-program and HUS Internet Therapy Compared to Treatment as Usual in Functional Disorders and Post Covid-19 Condition; <https://www.clinicaltrials.gov/study/NCT05212467>), using a benchmarking controlled trial approach (Malmivaara, 2015). To do so, encoded data will be transferred to the “acamedic” platform (see section 7.4 Confidentiality and coding).

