## **DiLCoS Substudy**

### ***Primary Endpoint***

The primary endpoint for DiLCoS will be the change in participants' functional capacity (T0 compared to T1), as measured by WHODAS 2.0 (12-item version; Üstün et al., 2010). This measure will provide a quantifiable assessment of the impact of the digital intervention on participants' daily functioning and disability levels.

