### ***Secondary Endpoints (see also Appendix 1)***

**Psychometric Questionnaire Data:** Questionnaires employed within BaLCoS to evaluate mental health status, quality of life and other psychosomatic factors will offer insights into the broader impact of the intervention and provide data for the longevity of possible effects emerging from DiLCoS.

**Neurocognitive Testing:** Neurocognitive function, which can be affected in PCC, will be assessed as a secondary endpoint. CNS Vital Signs (CNSVS, <https://www.cnsvs.com/>) will be assessed within BaLCoS at baseline and T3. This will help in evaluating any cognitive improvements as a result of the digital intervention.

**Measures of Physical Performance:** Physical performance metrics, measured at baseline and T3 within BaLCoS, assess improvements in physical health and capacity, which are critical components of overall recovery in PCC. Possible changes in physical performance metrics can provide insight into the effectiveness of exercises, especially physical elements, within DiLCoS.

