## Appendix 1: Schedule of assessments

|          | Outcomes/Parameters assessments                                                        | T0 |   | Additional visits          | T1 | T2 | T3 |
|----------|----------------------------------------------------------------------------------------|----|---|----------------------------|----|----|----|
|          |                                                                                        | 1  | 2 |                            |    |    |    |
| 0 | Oral and written information, written consent, screening inclusion-/exclusion criteria | x  |   |                            |    |    |    |
| 1 | Routine clinical information/assessment                                                | x  |   | depending on clinical need |    |    |    |
| 2 | Blood specimens (see Appendix 2)                                                       | x  |   |                            |    |    | x  |
| 3 | Neurocognitive PC test battery: CNSVS                                                  | x  | * |                            |    |    | x  |
| 4 | Psychometric Questionnaires                                                            |    |   |                            |    |    |    |
| a | Primary Outcome functional capacity: WHODAS 2.0 (12-item version)                      | x  |   |                            | x  | x  | x  |
| b | VAS: quality of life, symptom intensity, functional impairment, work ability           | x  |   |                            | x  | x  | x  |
| c | Life quality: EuroHIS QOL-8                                                            | x  |   |                            | x  | x  | x  |
| d | Symptoms: SSD-12, PHQ-15                                                               | x  |   |                            | x  | x  | x  |
| e | Depression: PHQ-8                                                                      | x  |   |                            | x  | x  | x  |
| f | Anxiety: GAD-7                                                                         | x  |   |                            | x  | x  | x  |
| g | Resilience: RS-11                                                                      | x  |   |                            | x  | x  | x  |

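### Section 4.1 includes the secondary endpoints in the DiLCoS primary analysis, in conflict with the single primary endpoint of section 2.2 and Appendix 1 and with a sample size that covers one test

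*Protocol*

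**What the plan says.** Section 2.2 of the protocol (DiLCoS Substudy, Primary Endpoint) names one endpoint: "The primary endpoint for DiLCoS will be the change in participants' functional capacity (T0 compared to T1), as measured by WHODAS 2.0". The schedule in Appendix 1 gives that status to one row only: "Primary Outcome functional capacity: WHODAS 2.0 (12-item version".

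Section 2.2 lists three groups of secondary endpoints. The first is the BALCoS questionnaires, which "will offer insights into the broader impact of the intervention and provide data for the longevity of possible effects emerging from DiLCoS". The other two are neurocognitive testing (CNSVS) and physical performance. Section 2.2 and Appendix 1 place both of these at baseline and T3, with nothing at T1.

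Section 4.1 (DiLCoS Substudy) then says: "The primary analysis is a pre-post comparison of the primary and secondary endpoints", "with T0 as a pre-intervention measure and T1 as a post-intervention measure". It reserves the term secondary analyses for the T2 and T3 follow-up and for an optional comparison with a non-randomised control group.

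Alpha is given once, as 0.05, in the power calculation of section 4.1. That calculation assumes power 0.80 and f = 0.15 in a repeated-measures, "within factors ANOVA with two time points resulted in" 105 participants, with 15% dropout included.

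**The concern.** Section 2.2 separates one primary endpoint from the rest, and section 4.1 puts them together again under the heading of primary analysis. The paragraph that follows does not repair this, because it assigns the secondary label to other time points and another comparison. The T0-T1 tests of the secondary questionnaires are therefore left in the primary tier.

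One stated aim of the substudy is proof of concept on effectiveness (section 2.1). If WHODAS showed no change and one other questionnaire reached p < 0.05, a report could truthfully call that a significant result of the prespecified primary analysis. The alpha and power in section 4.1 do not describe such a claim.

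There is also a practical fault. A T0-T1 comparison of the secondary endpoints cannot include CNSVS or physical performance, because neither is measured at T1.

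**Working it through.** **1. What the stated sample size pays for.** Inputs from section 4.1: f = 0.15, alpha = 0.05, power 0.80, m = 2 time points, dropout 15%. The T0-T1 correlation rho is not stated, so 0.5 is assumed. The test is a within-factor F test with 1 and n - 1 degrees of freedom and noncentrality

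lambda = n × m × f² / (1 - rho).

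At n = 90, lambda = 90 × 2 × 0.0225 / 0.5 = 8.1 and power is 0.804. At n = 89 power is 0.799, so 90 evaluable patients are needed. Allowing for dropout gives 90 / 0.85 = 105.9, or 90 × 1.15 = 103.5 with the simpler inflation. Both agree closely with the stated 105. Other values of rho do not: 0.4 gives 107 evaluable and 126 enrolled, and 0.6 gives 72 and 85. The stated N is thus what one test at 0.05 requires if rho is about 0.5. With two levels, the F test is equivalent to a two-sided paired t test.

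**2. How many scores can enter a T0-T1 comparison.** Rows of Appendix 1 marked at both T0 and T1:

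| Row | Scores |
|---|---|
| WHODAS 2.0 | 1 |
| VAS (quality of life, symptom intensity, functional impairment, work ability) | 4 |
| EuroHIS QOL-8, SSD-12, PHQ-15, PHQ-8, GAD-7, RS-11, ISI, CFS | 8 |
| **Total** | **13** |

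The Perceived Stress Scale is described in section 3.3 but has no row in Appendix 1; counting it gives 14. Adding the eight EMA items gives 22. CNSVS and physical performance are not counted, because they have no T1 measurement.

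**3. Chance of at least one false positive** if each of the 13 scores is tested at 0.05 and none has truly changed. For independent tests it is 1 - 0.95^13 = 1 - 0.513 = 0.487. For correlated tests it comes from simulating equicorrelated two-sided z tests with critical value 1.96 (300,000 draws per setting). The correlations are assumptions.

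| Correlation | 13 tests | 14 tests | 22 tests |
|---|---|---|---|
| 0 | 0.487 | 0.512 | 0.675 |
| 0.3 | 0.419 | 0.438 | 0.569 |
| 0.5 | 0.334 | 0.349 | 0.438 |
| 0.7 | 0.241 | 0.248 | 0.300 |
| 0.8 | 0.192 | 0.197 | 0.232 |

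**4. What it would cost to keep all 13 tests confirmatory.** Bonferroni gives 0.05 / 13 = 0.00385 per test. At 90 evaluable patients (f = 0.15, rho = 0.5) power falls from 80% to about 46%. Restoring 80% takes 159 evaluable patients, and 159 / 0.85 = 187.1, so 188 enrolled. The stated 105 does not support that reading of section 4.1.

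**The case against.** The strongest reply is that the ranking never disappears. The sentence in section 4.1 still speaks of primary and secondary endpoints and refers back to section 2.2. On this view, primary and secondary analysis merely sort the comparisons: pre-post first, then follow-up and the control group. The substudy is a single-arm proof-of-feasibility study, and section 2.1 says that it will explore effects.

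Much of this stands, and it limits the point:

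- A reader might infer that all 13 scores share decisive status. The documents do not support that. No rule makes success on any one endpoint a positive result, and WHODAS is still the only endpoint called primary.
- A reader might take about one in three as the substudy's error rate. It is not. It needs an assumed correlation of 0.5 and a reading in which any significant score is confirmatory. The protocol never promises a 5% family-wise rate, and the WHODAS test keeps its own 5%.
- A reader might count the lack of a multiplicity procedure as a fault. Such detail is commonly left to a statistical analysis plan, which is not at hand, so its absence here is no finding.
- In an uncontrolled pre-post design, even a sound alpha does not separate the intervention's effect from change over time, so the gain from tidier testing is limited.

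The wording conflict remains. Section 4.1 states what the primary analysis contains, and an analysis plan would have to contradict that sentence to agree with section 2.2. Nor does sorting by comparison explain how endpoints without a T1 measurement enter a T0-T1 analysis.

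**Conclusion.** The point holds as a conflict within the protocol. Section 4.1 gives the DiLCoS primary analysis a content that does not fit the single primary endpoint in section 2.2 and Appendix 1, does not fit a sample size that matches one test at 0.05 (at an assumed T0-T1 correlation of 0.5), and cannot be carried out for CNSVS and physical performance.

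The size is conditional. If any significant result among the 13 scores were treated as confirmatory, the chance of at least one false positive would be 19% to 49% over assumed correlations from 0.8 to 0. Nothing is wrong with the WHODAS test itself. The correction is worth making because it is nearly free and closes off a misleading report of the results.

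**What to change.** Replace the sentence in section 4.1 with wording to this effect: *The primary analysis is the change in WHODAS 2.0 from T0 to T1, tested at two-sided alpha 0.05. It is the only confirmatory test of effectiveness. T0-T1 changes in the other questionnaires, and baseline-T3 changes in CNSVS and physical performance, are secondary analyses; they are reported as estimates with 95% confidence intervals and labelled exploratory.*

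Add that the feasibility and usability aims of section 2.1 are judged separately. The WHODAS test should not be made the sole criterion for the substudy as a whole, since those aims stand beside it.

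The cost is a few lines of text. The sample size, data collection and patient burden stay as they are. The one small loss is that a significant secondary result can no longer be presented as a finding of the primary analysis.

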## **2.3 Project design**

This is a single-center, observational registry-based cohort study. The study site will be located at the medical outpatient clinic unit at the UHB, which has started a service specializing in PCC patients in 2021 due to the high demand in the population. This service collaborates with experts from numerous disciplines relevant for managing PCC patients, including e.g. cardiology, neurology, pneumology, otorhinolaryngology, psychosomatic medicine, and physiotherapy. All patients visiting the PCC speciality clinic at the UHB

- i. will be invited to participate in BALCoS. To this end, they will also be asked to provide informed consent that
- ii. data collected within BALCoS and
- iii. data from their routine clinical care can be used for future research purposes. Further,
- iv. patients will be asked to give consent that they can be recontacted for potential additional follow-up assessments

Please note that ii to iv are no prerequisite for participating in BALCoS and that i is no prerequisite for iii and iv.

We will further get in touch with physicians from other PCC consultations from the German-speaking parts of Switzerland and the neighbouring Germany and will ask them to advertise the study in their consultation.

BALCoS is primarily funded by the Swiss State Secretariat for Education, Research and Innovation (SERI, under funding number: 22.00094) in the context of a European Union (Horizon Europe) research consortium “Long Covid” (funding number: 101057553). Data collected within BALCoS will be analyzed on its own, but will also contribute to a geographically diverse pooled data set derived from studies involved in the above-mentioned EU/SERI funded consortium, i.e., biospecimens being sent and data being shared (refer to appendix 2 and Joint Controllershship Agreement). Data from all the EU consortium (from The Netherlands, Finland, and Switzerland) shall be used to develop an AI-driven prediction tool for clinical decision support and shared decision-making (please also refer to the Joint Controllershship Agreement).

Prospectively, approximately 6 months after data collection has started, new patients included in BALCoS are invited to participate in the DiLCoS substudy, a proof-of-feasibility substudy of a digital intervention with personalized, multimodal digital interventions. The initial protocol has been amended to comprise the DiLCoS substudy.

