#### **DiLCoS Substudy**

Participants enrolled in BALCoS who have completed the baseline measurements, but not yet T1 measurements, are asked to participate in the DiLCoS substudy. Due to a decrease in PCC referrals, patients who are further progressed in BALCoS (beyond T1) will also be invited to take part in the intervention. To evaluate their participation in the intervention, they will again complete the measures described in section below (with the last measure completed within 3 months before the start of the intervention being the new BL). Their refusal of participation in DiLCoS or withdrawal of consent during participation in DiLCoS does not affect their participation in BALCoS in any manner. There is one additional inclusion criterion for the DiLCoS substudy, which is the possession of a smartphone with an operating system that is compatible with software comprising the intervention. For being included in the DiLCoS substudy, separate signed informed consent is required (see separate document).

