### **DiLCoS Substudy**

The DiLCoS substudy usually starts after participants have completed the baseline (T0) measurements of the BALCoS study and before the T1 measurements. This timing ensures that the impact of the digital intervention can be isolated and accurately assessed within the broader scope of BALCoS. Due to a decrease in PCC referrals, patients who are further progressed in BALCoS (beyond T1) will also be invited to take part in the intervention. To evaluate their participation in the intervention, they will again complete the measures described in section above (with the last measure completed within 3 months before the start of the intervention being the new BL). As part of the onboarding process, participants will receive a text message sent from the DocDok system (see 7.3. Overview of the DocDok system) inviting them to install the docdok smartphone application from the Google Play Store or the iOS App Store. Included in this text message is an initial password for logging into the docdok smartphone application. Only with this password which is generated after patients are added to the study, patients can access the content of the application. After initial login, participants choose their own password and login with their personalized password from that moment. The smartphone application is equipped with a standard password renewal function, that allows participants to change their password if they have forgotten it. The study personnel facilitating the onboarding process will explain the structure of the digital intervention by going through a demonstration module together with the participant and answering questions/addressing concerns raised by the participant. The demonstration module contains a summary of the type of content that patients will receive during the intervention and a description of the structure of each module. Additionally, the module contains the remark that the primary aim of the smartphone application is clinical research. Patients are also reminded that they should contact the study personnel whenever they feel uncomfortable with an exercise and that they can skip or stop exercises at any point of the intervention. After completion of said demonstration, the participant and the study team will decide an appropriate starting date, with possible start days to be either Thursday or Friday.

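### The treatment-as-usual group in section 4.1 can overlap with the DiLCoS group now that patients beyond T1 are invited, so patients and measurements can count on both sides

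*Protocol*

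**What the plan says.** Section 4.1 (DiLCoS Substudy) states that "a comparative analysis (DiLCoS - treatment as usual) may be performed". It forms the comparator from two sources. The first is "Patients who participated in the BALCoS study before the initiation of the DiLCoS substudy". The second is given as "patients who agree to participate in BALCoS but do not give consent to participate in DiLCoS will be considered as a non-randomised control group". On the model it says: "With these two groups, generalized mixed models will be calculated to assess both within- as well as between-patient changes".

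Section 2.3 describes the substudy's entry rule as one for new enrollees: "new patients included in BALCoS are invited to participate in the DiLCoS substudy". Sections 3.1 and 3.3 go further. Because referrals fell, "patients who are further progressed in BALCoS (beyond T1) will also be invited to take part in the intervention". Section 3.3 has these patients go through the assessments a second time. Both sections fix the starting point of that second series in the same way: "with the last measure completed within 3 months before the start of the intervention being the new BL". Section 3.4 foresees that some patients will go through all measures twice and be compensated twice.

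Section 3.2 puts the first BALCoS patient in February 2023. Section 4.1 puts the first DiLCoS patient in March 2024.

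**The concern.** The first control source is separate from the DiLCoS group only if DiLCoS takes new enrollees alone, as section 2.3 describes. Once patients beyond T1 may join, the early enrollees who make up that source are among those invited. Section 4.1 was not adapted: it neither removes later joiners from the control group nor ends their control follow-up at app start, and it does not say on which side a shared measurement counts.

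The primary analysis is single-arm, so this comparison is the only one within the study that can separate an effect of the app from natural recovery. Section 4.1 gives it that purpose. If the definition is followed literally, some app-exposed visits are labelled treatment as usual and some patients sit in both groups. If it is not followed, someone must decide after the data are in whether to keep, drop or split the late joiners.

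**Working it through.** **1. The plan's own figure.** Section 4.1 gives N=105 for the pre-post analysis: f = 0.15, two time points, power 0.80, alpha 0.05, 15% dropout. The correlation between time points is not stated; take rho = 0.5.
- Noncentrality: lambda = f² × m × N / (1 − rho) = 0.0225 × 2 × N / 0.5 = 0.09 N, with 1 and N − 1 degrees of freedom.
- N = 90 gives power 0.804; N = 89 gives 0.799.
- Dropout: 90 / 0.85 = 105.9. In reverse, 105 × 0.85 = 89.25.

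The stated 105 is reproduced to within rounding. No control group enters this calculation, so the present point does not change it.

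**2. The two definitions side by side.**

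| Patient | Control under 4.1? | May join DiLCoS under 3.1 and 3.3? |
|---|---|---|
| Enrolled before March 2024, beyond T1 | Yes, first source | Yes, with a new baseline |
| Enrolled after DiLCoS start, declines | Yes, second source | Has declined |
| Enrolled after DiLCoS start, consents | No | Yes |

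The first row is in both columns, and nothing in 4.1 resolves it.

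**3. What happens to a late joiner's measurements.**
- First-schedule T0 and T1: completed before the app, so the T0-T1 change is genuine untreated data.
- Latest assessment before app start: it can be a control visit and also the new DiLCoS baseline, so it can count twice.
- Any first-schedule T2 or T3 visit after app start: exposed follow-up from a patient who is a control by definition.
- Patients whose T3 preceded app start contribute only untreated first-schedule data, but still appear in both groups.

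**4. Size of the first control source.** February 2023 to March 2024 is about 13 months; February 2023 to March 2025 is 25 months.
- At the section 3.2 expectation of at least 120 patients, spread evenly: 120 × 13 / 25 ≈ 62.
- At the section 4.1 rate of 136 per year: 136 × 13 / 12 ≈ 147.

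The protocol gives no share that later joins. If 10% to 30% did (assumption), 6 to 19 of 62, or 15 to 44 of 147, would meet both definitions.

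The recruitment targets give a rough bound. With 120 patients, about 120 − 62 = 58 enrol after DiLCoS starts. If all of them joined, reaching 105 would still need 105 − 58 = 47 early patients, and 47 / 62 = 76%. At 136 per year, the 12 months to March 2025 bring 136 new patients; if all joined, no early patient would be needed. The requirement therefore runs from 0% to 76%, depending on recruitment. This is not a forecast: not every early patient is reachable or owns a compatible smartphone.

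**5. Dilution at T2 or T3.** Let D be a constant difference between exposed and unexposed patients at a visit, and p the share of control values at that visit taken after app start. The control mean moves by p × D, so the observed contrast is D − p × D = (1 − p) × D.
- p = 0.10: 90% of D remains.
- p = 0.20: 80% remains.
- p = 0.30: 70% remains.

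Here p refers to the whole control series, decliners included, so a given share of crossover among early enrollees gives a smaller p.

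**The case against.** The comparison is optional, secondary and openly non-randomised, in a feasibility substudy whose primary analysis does not use it. Section 4.1 calls the comparator treatment as usual, and sections 3.1, 3.3 and 3.4 give late joiners a fresh series of measures. A sensible analyst would probably not count app-exposed visits as control. Exposure coding is also often left to a statistical analysis plan. All of this limits the weight of the point. It does not remove it, because the protocol does not leave the group definition open: it states one, and that definition conflicts with its own entry rule.

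Three stronger readings go too far:
- A reader might infer that the T0-T1 contrast, or the effect behind N=105, is diluted. For patients beyond T1 the first T0-T1 interval was complete before any exposure. A few early enrollees still between T0 and T1 when DiLCoS opened could differ, but they are not the group the widened rule adds.
- A reader might infer a definite loss of power. The protocol gives no control-group size, no crossover share and no between-group effect; f = 0.15 belongs to the single-arm calculation. No power figure for this comparison can be supported.
- A reader might infer that the named model cannot handle patients who change group. Generalized mixed models can, with time-varying exposure and a patient effect. The difficulty is the fixed two-group label, not the model class.

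Nor is this the only comparative evidence foreseen: section 4.1 also mentions benchmarking against another consortium study.

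**Conclusion.** The point holds as a definitional conflict between section 4.1 and sections 3.1 and 3.3. Early BALCoS enrollees can meet both group definitions, one measurement can serve on both sides, and first-schedule T2 or T3 visits after app start would be labelled control. The overlap of patients affects every contrast in the comparison; dilution affects T2 and T3 only. Its size is proportional to the share of control values taken after app start: 10% to 30% leaves 90% to 70% of a constant contrast. That share is an assumption, and the calculation also assumes a constant difference and that 4.1 is applied literally. The primary analysis and the sample size stand. This should be corrected before the comparison is run, but it does not threaten the substudy's main result.

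**What to change.** In section 4.1, replace the fixed group label with exposure by date:
- Control time is all BALCoS follow-up up to a patient's DiLCoS start, including that of later joiners, plus all follow-up of decliners.
- DiLCoS time is all follow-up from the start date on.
- Each measurement enters once. An assessment that serves as the new baseline precedes app start and counts as unexposed.
- Fit one mixed model with exposure as a time-varying term, a patient random effect and adjustment for time since BALCoS baseline.

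Restricting controls to patients who never join would also remove the overlap, but it selects controls on a later decision; the documents do not allow the direction of that bias to be judged. Exposure by date keeps the untreated follow-up of later joiners.

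The cost is one paragraph and slightly more complex modelling. Section 3.3 already has a start date agreed with each participant, so the exposure variable needs only that date in the analysis file; no extra patients or visits are needed. The comparison remains non-randomised, and the text should say so.
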